# Immersive Reality–Based Training Simulator for Dental Extraction: Protocol for a Randomized Pilot Trial

**DOI:** 10.2196/74978

**Published:** 2025-11-05

**Keywords:** dental extraction, immersive reality, pilot trial, virtual training, study protocol

## Abstract

**Background:**

Dental students’ competencies are shaped by their training, yet traditional methods with mannequins often lack the depth necessary for comprehensive understanding, potentially impacting clinical proficiency. Immersive reality (IR) innovatively offers interactive and scenario-based environments that may enhance skill acquisition.

**Objective:**

This study evaluates the effectiveness of IR-based training implementation in comparison with conventional training methods for dental extractions.

**Methods:**

A prospective multicenter randomized clinical trial was conducted. Students were randomized to either IR-based training on open and closed extractions or conventional hands-on tutorials by oral surgeons. Post training, participants’ satisfaction and understanding were assessed and analyzed.

**Results:**

As of September 2025, 60 students from Hasanuddin University, Makassar, and Padjajaran University, Bandung, have been enrolled, and study enrollment will be expanded to Universitas Sumatera Utara, Medan. Data collection is ongoing and will conclude in November 2025, with expected dissemination in early 2026.

**Conclusions:**

IR-based training offers a novel approach that may boost motivation, knowledge retention, and skill transfer in dental education. This pilot protocol explores IR’s feasibility and potential to advance dental students’ competencies.

**Trial Registration:**

Indonesian Clinical Research Registry INA-QES4CC5; https://ina-crr.kemkes.go.id/en/studi/207

**International Registered Report Identifier (IRRID):**

DERR1-10.2196/74978

## Introduction

Dental extraction is among the most frequently performed procedures in dental practice [1]. Indications for extraction are diverse, including periodontitis, endodontic complications, orthodontic needs, ectopic eruption, prosthetic treatment planning, traumatic injury, and systemic conditions, with dental caries being the most common cause [2-4]. The high prevalence of extractions underscores the importance of equipping dental students with sufficient knowledge, technical proficiency, and clinical competence [5,6].

Conventional training methods and passive observation restrict students’ ability to understand the complexity of treatments, particularly within the confined working environment of the oral cavity [7,8]. Moreover, novice dental students often lack familiarity with assisting tasks, reducing training efficiency and learning outcomes. Effective skill acquisition requires not only theoretical knowledge but also spatial imagination, active engagement, and repeated practice opportunities [9-11]. Consequently, extensive training and prolonged clinical exposure are often necessary before dental students achieve the level of competence required to provide safe and effective oral health care [12,13].

Immersive reality (IR), which integrates virtual reality and augmented reality, has emerged as a promising educational technology to overcome these challenges [14-17]. IR provides a safe, realistic, and hands-on platform for students to practice clinical procedures and refine their skills [18-25]. Evidence suggests that IR-based training improves practical competence, treatment planning, and standardized assessment while offering repeatable and engaging learning experiences [26-30]. Importantly, IR technology supports consistent training for complex procedures that demand precision and manual dexterity [31-33]. By addressing limitations of conventional learning—such as high costs, limited patient cases, and restricted opportunities for repeated practice—IR can bridge gaps in skill acquisition, foster collaboration, and enhance creativity in clinical training [34-38].

Despite these advantages, the application of IR as a simulator for dental extraction training remains insufficiently explored. To date, IR technology has been implemented in operative dentistry, periodontology, and dental radiography for practices such as tooth drilling, endodontic cavity access, crown placement, and periodontal procedures [39-43]. Furthermore, none of these applications involves students from multicenter institutions. This study seeks to highlight the use of IR training for dental extractions involving students from multicenter institutions while also generating feedback for further refinement of the simulator and its associated training protocol.

## Methods

### Apparatus

Unity 3D Engine software (Microsoft Corporation) was used as the platform for simulating dental extraction procedures in an IR environment. This platform enables users to engage from a first-person perspective. In the virtual environment, users can interact with 3D models by using either hand gestures or controllers.

In this study, the IR hardware setup consists of a personal computer featuring an Intel Core i7-11800H chipset and an NVIDIA GeForce RTX 3080 graphics card, which includes a GPU with 10 GB of GDDR6X memory. The configuration also incorporates a Meta Quest Pro 3 (Reality Labs) head-mounted display (HMD). The equipment enables Unity to run at a constant frame rate of over 60 frames per second using the “high quality” display settings of the HMD.

### Trial Design and Study Population

#### Overview

This protocol is for a prospective multicenter randomized clinical trial, which began in March 2025 and is expected to end in November 2025. This protocol outlines our plan to assess the knowledge and skill enhancement of a pilot intervention across three centers: Hasanuddin University (Makassar, Indonesia), Padjajaran University (Bandung, Indonesia), and Universitas Sumatera Utara (Medan, Indonesia). A total of 90 dental students participated in the study (G*Power effect size 0.6, statistical power 85%). All participants enrolled in this study were randomly assigned to either an intervention group (n=15) or a control group (n=15) within each center. We used the block randomization method for the allocation of participants.

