#### Participants’ Performance and Knowledge Improvement

To assess the practical skills and knowledge acquired, participants from both the intervention and control groups will be required to complete a pretest prior to the training and a posttest following the training session. The MCQs were administered in accordance with the reference textbook used by the Faculty of Dentistry, as outlined in the dentistry curriculum [46]. The scores ranged from 0 to 100, and the test scores of both groups were subsequently compared. The MCQs are centered on the procedural steps, instrumentation, and guiding principles pertinent to dental extraction. This examination is an established component of the curricula at Hasanuddin University, Padjajaran University, and Universitas Sumatera Utara, aimed at assessing students’ practical competencies and theoretical knowledge. Consequently, a comparative analysis test will be used to evaluate the scores obtained from the clinical skill training between these two groups.

Additionally, the performance of participants will be evaluated through recorded video training and will be assessed by an independent reviewer, focusing on training time completion, in-app lag or confusion, and skipped steps. The confidential paper-based data of participants will be securely stored in a locked storage unit at the study site, while electronic data will be maintained in a protected folder on a server at Hasanuddin University, Makassar, Indonesia.

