### Data Analysis Plan

The data were analyzed using SPSS v.22 (IBM Corp). Both descriptive statistics (frequency, percentage, mean, and SD) and inferential statistics (multivariate ANOVA) were used. A *P* value less than .05 was considered statistically significant.

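### The sample-size figures (90 students, effect size 0.6, 85% power) do not fit together as stated; a conventional two-sided comparison gives about 80%

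*Protocol article*

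**What the plan says.** The Overview under Trial Design and Study Population gives the whole justification: "A total of 90 dental students participated in the study (G*Power effect size 0.6, statistical power 85" per cent. The same paragraph sets the allocation as "an intervention group (n=15) or a control group (n=15) within each center", with three centers.

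The significance level appears only in the Data Analysis Plan, where a P "value less than .05 was considered statistically significant". That section names a single inferential method: "inferential statistics (multivariate ANOVA) were used". The section on performance and knowledge improvement describes a multiple-choice test scored 0 to 100 before and after training, and says that "the test scores of both groups were subsequently compared".

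The power sentence does not name the test, the metric of the effect size, the number of sides, the endpoint or any allowance for losses.

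**The concern.** An effect size, a power and a sample size are tied together once the test and the significance level are set. The article prints all three, and they do not agree under the usual test for two independent groups.

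The article uses this sentence to support 90 students in a trial whose stated objective is to compare the effectiveness of two training methods. If the true power at 0.6 SD is nearer 80%, the type II error is about 20% rather than the implied 15%, a third larger. A non-significant result would then be taken as stronger evidence against a 0.6 SD effect than it is. A reader also cannot tell which comparison the 85% belongs to.

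**Working it through.** **Inputs**

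- Total 90, effect size 0.6, power 85%: Overview.
- Per arm: 3 centers × 15 = 45 (Overview).
- Alpha 0.05: Data Analysis Plan. It is not repeated in the power sentence.
- Test, metric and sides: not stated. The readings below are assumptions.

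**1. Two-sided two-sample t test, 0.6 read as Cohen's d**

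Noncentrality = d × √(n/2) = 0.6 × √(45/2) = 0.6 × 4.743 = 2.846. Degrees of freedom = 2 × 45 − 2 = 88. The two-sided 5% critical value is 1.987. Power from the noncentral t distribution is **80.4%** (normal approximation 81.2%). A two-group ANOVA with f = d/2 = 0.3 is the same test and gives the same 80.4%.

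Smallest n per arm with at least 85% power: 51 (85.1%), since 50 gives 84.4%. Total 2 × 51 = **102**. The normal approximation gives 50 per arm, total 100.

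Difference detectable with 85% power at 45 per arm: d = 0.639, about **0.64**.

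**2. One-sided t test, d = 0.6**

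The critical value is 1.662. Power at 45 per arm is **88.1%**. For 85%, 41 per arm are needed, total 82. Adding 10%: 82 × 1.10 = 90.2. Dividing by 0.90: 82/0.90 = 91.1. Rounded up, that is 91 or 92. The normal approximation (40 per arm, total 80) gives 80/0.90 = 88.9, so 89.

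**3. ANOVA with two groups, 0.6 read as f**

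Noncentrality = f² × N = 0.36 × 90 = 32.4. Power exceeds **99.9%**, and 85% would need a total of only 28. Reading 0.6 as f² implies f = √0.6 = 0.775, which is further away still.

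**4. Other settings that the article does not state**

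- One-sided Mann-Whitney at 45 per arm: 86.7% with asymptotic relative efficiency 3/π, 83.6% with the minimum of 0.864. Two-sided: 78.5% and 74.3%.
- ANCOVA of the posttest on the pretest, two-sided. The effective difference is 0.6/√(1 − r²), where r is the pre-post correlation. At r = 0.30 it is 0.629 (power 83.9%), at r = 0.34 it is 0.638 (84.9%), at r = 0.35 it is 0.641 (85.2%), and at r = 0.40 it is 0.655 (86.7%).

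| Reading (alpha 0.05) | Power at 90 | Total for 85% |
|---|---|---|
| Two-sided t, d = 0.6 | 80.4% | 102 |
| One-sided t, d = 0.6 | 88.1% | 82 |
| ANOVA, f = 0.6, two groups | >99.9% | 28 |

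**5. Losses, for illustration only**

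The article gives no loss rate. If the intervention arm fell to 40 against 45, two-sided power at d = 0.6 would be 77.9%. At 36 against 45 it would be 75.5%.

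**The case against.** The best defence is that the power sentence is incomplete rather than wrong. Because test, metric and sidedness are not given, 80% and 102 follow from one reading among several. A one-sided t test with a 10% add-on lands at about 90, and would leave about 85% power with 82 students analysed. The software output may therefore have been right for settings that were never printed. The trial is labelled a pilot, two centers have already enrolled 60 students, and a journal article may leave the full calculation to another document.

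Much of this stands. The documents do not show that the design definitely delivers 80%, nor that the calculation was carried out wrongly. What does not stand is the sentence as printed. Each route to about 85% adds something unstated, and the one-sided routes do not match multivariate ANOVA, which is a non-directional test. The pilot label does not help either, because the power figure is itself offered as the justification for 90.

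Two stronger readings are tempting and unsupported:

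- *Multivariate ANOVA necessarily has less power than a single comparison.* It depends on the outcomes and their correlation, and the article does not list the dependent variables. Take two outcomes, 45 per arm and Hotelling's T². If only one outcome differs by 0.6 SD, power is 70.7% at correlation 0, 83.2% at 0.5 and 94.9% at 0.7. If both differ by 0.6 SD, it is 95.3% at correlation 0 and 83.2% at 0.5.
- *Losses will cut power by a known amount.* The exclusion and adverse-event sections remove students who have cybersickness or, under the exclusion criteria, do not complete training. They give no rate and do not say whether such students are replaced. The figures in step 5 show only the direction and rough scale.

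**Conclusion.** The point holds in this form: 90 students, effect size 0.6 and 85% power are not mutually consistent on any plain reading of what the article states. Under the conventional reading (two-sided two-sample t test, alpha 0.05, Cohen's d of 0.6, 45 analysed per arm), power is about 80%. That is 4.6 percentage points below the stated figure, and 85% would need 12 more students or a difference of about 0.64 SD. The arithmetic is firm; the choice of test, metric and sides is an assumption.

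A one-sided test with about 10% for losses is a possible origin of the figures. If that is what was done, the fault is an undeclared one-sided design that does not match the planned analysis. Either way the sentence needs correcting, and the size of the trial does not.

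**What to change.** Keep 90 students and replace the power statement with, for example: *45 per arm gives 80% power (two-sided alpha 0.05, two-sample comparison of posttest multiple-choice scores) for a standardised difference of 0.6, or 85% for 0.64.*

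Alternatively, if the posttest is to be analysed by ANCOVA adjusted for the pretest, state that 85% power at 0.6 requires a pre-post correlation of about 0.35, and name that model in the Data Analysis Plan.

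If the sponsor used a one-sided test, another metric or an allowance for losses, state it and bring the analysis into line with it. Any power quoted for unequal losses should be labelled illustrative.

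The cost is one sentence, plus a matching line in the Data Analysis Plan if the test changes. No further students are needed. On the conventional reading, the stated power becomes less favourable.

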#### Intervention Group

Before the intervention, two oral and maxillofacial surgeons from each center will follow a comprehensive meeting held in Hasanuddin University, Makassar, to ensure consistent delivery of the interventions across centers and instructors. In addition, a facility assessment will be reported during the meeting to ensure that each center can deliver the intervention method using the same protocol.

Participants will be given a brief introduction and explanation of the study’s purpose. A research assistant will present the informed consent both in writing and verbally. This study has adopted standardized procedures for tooth extraction, using both open and closed methods.

The IR training session will be conducted in a standing position, where participants role-play as dentists. The training session will focus on open and closed dental extraction for the first molar tooth (tooth 46), supervised by two oral and maxillofacial surgeons in each center. For all training sessions, the first 10 minutes will be conducted under direct supervision. Participants will then continue their sessions for the last 40 minutes using in-app assistance (sound, highlighted areas, and arrows) without additional support for the remaining session.

The IR HMD wirelessly streams to an external device and will be used during the first session to monitor the participants’ training execution and provide guidance when necessary. Participants were required to complete a full round of training. This procedure included several steps: administering local anesthesia, making an incision and separating the tooth (in open method extraction mode), luxating and extracting the tooth, performing curettage, irrigating the wound, and suturing.

Following the completion of the procedure, participants are presented with the option to either restart the training sessions by selecting the reset button or terminate the session by choosing the exit button located in the menu area.

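### Allocation is balanced 15:15 within each of three centres, but the stated analysis names no centre term; adding centre is a free gain in precision if scores differ by centre

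*Protocol article*

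**What the plan says.** The Overview under Trial Design and Study Population describes a study to "assess the knowledge and skill enhancement of a pilot intervention across three centers". Participants are "randomly assigned to either an intervention group (n=15) or a control group (n=15) within each center", and the method is stated as "We used the block randomization method for the allocation of participants". Centre is therefore a stratum of the randomisation, and the arms are balanced on it at 45 v 45 overall.

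The Data Analysis Plan section says that "inferential statistics (multivariate ANOVA) were used", with a P "value less than .05 was considered statistically significant". It lists no factors, outcomes or covariates. The section on performance and knowledge improvement adds that "a comparative analysis test will be used to evaluate the scores obtained from the clinical skill training between these two groups". Centre is not mentioned in either place.

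On delivery, the immersive-reality sessions are "supervised by two oral and maxillofacial surgeons in each center". The Control Group section likewise has two surgeons guiding the training at each centre.

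**The concern.** When allocation is forced to be equal within each centre, centre differences cancel out of the difference between arms. An analysis without centre does not know this and counts the same differences as residual noise. The reported standard error is then larger than the true sampling variability, the P value is conservative and power is lost.

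Centre differences are plausible. The students come from three universities in different provinces, each centre has its own surgeons, and the third centre had still to recruit when the other two had enrolled 60 students. The article also presents the multicentre feature as what is new about the study, yet the analysis as described makes no use of it.

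What is at stake is precision. The estimated arm difference is not biased by leaving centre out.

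**Working it through.** **Inputs.** From the document: 3 centres, 15 v 15 in each, effect size 0.6 (type not stated, taken as a standardised mean difference), alpha 0.05 (sidedness not stated, taken as two-sided). Assumed: the share *p* of total score variance that lies between centres, from 0 to 30%. Total SD is set to 1, with no clustering by arm within centre and no pretest in the model.

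**The plan's own figure.** The article states "A total of 90 dental students participated in the study (G*Power effect size 0.6, statistical power 85"%). With 45 per arm, a two-sided t test at 0.6 SD has power 0.80, and 85% would need 102 students. One-sided, 82 would be enough. The stated combination is not reproduced from the stated inputs. That is a separate matter and does not bear on this point. Power of 0.80 serves as the starting value below.

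**True variability of the arm difference.** Centre effects cancel, so SD = √(2(1−p)/45).

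**Standard error when centre is left out.** The pooled within-arm variance picks up the centre spread.
- Centre means fixed at exactly share *p*: each arm gains a sum of squares of 15 × 3 × p = 45p on 44 df, so the variance is (1−p) + 45p/44.
- Centre means drawn at random: the expected squared deviations of three draws sum to 2p, so the gain is 30p and the variance is (1−p) + 30p/44.
- In both cases SE = √(2 × variance/45).

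**Worked example, p = 10%, fixed centre means.**
- True SD = √(2 × 0.90/45) = 0.200.
- Variance without centre = 0.90 + 4.5/44 = 1.0023, so SE = √(2 × 1.0023/45) = 0.211. The ratio to the true SD is 1.055.
- The nominal cut-off of 1.987 (88 df) acts as 1.987 × 1.055 = 2.097. The two-sided tail beyond that (t, 86 df) is 3.9%.
- Power at 0.6: the noncentrality is 0.6/0.200 = 3.0. Against a cut-off of 2.097 this gives 0.815. With centre in the model the cut-off is 1.988 and power is 0.843.

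**Across the range.** Where a range is shown, the lower value is for fixed centre means (formula above) and the upper for random centre means (simulation, 40,000 trials per setting).

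| Centre share | True SD | SE without centre (fixed / random) | Type I error without centre | Power without centre | Power with centre |
|---|---|---|---|---|---|
| 0% | 0.211 | 0.211 / 0.211 | 5% | 0.80 | 0.80 |
| 5% | 0.205 | 0.211 / 0.209 | 4.4–4.6% | 0.81–0.82 | 0.82 |
| 10% | 0.200 | 0.211 / 0.207 | 3.9–4.4% | 0.82 | 0.84 |
| 20% | 0.189 | 0.211 / 0.204 | 2.9–3.8% | 0.83–0.85 | 0.88 |
| 30% | 0.176 | 0.212 / 0.201 | 1.9–3.1% | 0.84–0.87 | 0.92 |

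With centre in the model, type I error stays at about 5% throughout.

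**When the direction reverses.** Suppose each arm within a centre also has its own shared effect, with variance share τ, for example from arm-specific instructors or group sessions. Then the variance of the arm difference is 2(1−p−τ)/45 + 2τ/3. With p = 10% and τ = 2%, this is 0.0391 + 0.0133 = 0.0524, an SD of 0.229, while the SE without centre is only about 0.207. In simulation the type I error is then about 7.7% without centre and 8.9% with it. At τ = 1% the figures are about 5.7–5.9% and 6.6–6.9%. A centre main effect does not remove this kind of clustering.

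**The case against.** The strongest objection is that the article does not say centre is left out. The Data Analysis Plan names a method and lists no factors at all; arm is not named there either. An ANOVA that includes centre fits that sentence as well as one that does not, and a fuller analysis plan may exist. This stands against the stronger reading a reader might draw, that the trial's error bars are wrong. It does not remove the recommendation: the article fixes the stratified allocation and describes the comparison only as between two groups, and including the stratum is a concrete improvement, not a request for more detail.

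Second, a reader might infer that the same two surgeons teach both arms at a centre, so that instructor effects cancel. Neither the Intervention Group nor the Control Group section says so. If instructors are arm-specific, or sessions are shared, the standard error may be too small instead of too large. This also stands, and it makes the direction of the error conditional.

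Third, the centre share is assumed, and parts of the article point towards homogeneity: common eligibility criteria, a test established in the curricula of all three universities, a calibrated answer key, and a meeting to align delivery. At a 5% share the gain is only 1–2 points of power.

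Fourth, the pretest is absent from the calculation. Stable centre differences appear in both tests, so adjusting for the pretest would absorb part of them. The table therefore compares centre with nothing and overstates what centre adds beyond the pretest.

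**Conclusion.** The point holds in a conditional form. Allocation is balanced within centre and the stated analysis names no centre term. If mean scores differ by centre and there is no further clustering by arm within centre, leaving centre out makes the test somewhat conservative and loses power: nothing at a 0% share, 1–2 points at 5%, about 2–3 at 10%, and about 5–8 at 30%. These shares are assumptions, and the gain shrinks once the pretest is in the model.

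The documents do not support the unconditional reading that standard errors are too large and P values too conservative. That would require knowing that centre is excluded, that centres differ, and that nothing clusters by arm within centre; the article establishes none of the three. Under the stated conditions there is no inflation of false positives, and the estimate is not biased. This is a free improvement to the analysis, not a threat to the trial's validity.

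**What to change.** State the between-arm model for the multiple-choice score as posttest on arm, pretest and centre, with centre as a fixed effect at three levels. Show the arm difference for each centre descriptively, with intervals and without tests: at 15 v 15, power for 0.6 SD is only about 0.35. State also whether the same surgeons teach both arms at a centre and whether students are trained in groups, since a centre term does not deal with clustering by arm.

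The cost is one model term, 2 of 88 residual degrees of freedom before the pretest is added, and no new data. The article describes data collection as still running to November 2025, so the model should be fixed before the final comparison is run.
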